## Abstract

**Introduction:**

Cauda equina syndrome (CES) is a potentially devastating condition caused by compression of the cauda equina nerve roots. This can result in bowel, bladder and sexual dysfunction plus lower limb weakness, numbness and pain. CES occurs infrequently, but has serious potential morbidity and medicolegal consequences. This study aims to identify and describe the presentation and management of patients with CES in the UK.

**Methods and analysis:**

Understanding Cauda Equina Syndrome (UCES) is a prospective and collaborative multicentre cohort study of adult patients with confirmed CES managed at specialist spinal centres in the UK. Participants will be identified using neurosurgical and orthopaedic trainee networks to screen referrals to spinal centres. Details of presentation, investigations, management and service usage will be recorded. Both patient-reported and clinician-reported outcome measures will be assessed for 1 year after surgery. This will establish the incidence of CES, current investigation and management practices, and adherence to national standards of care. Outcomes will be stratified by clinical presentation and patient management. Accurate and up to date information about the presentation, management and outcome of patients with CES will inform standards of service design and delivery for this important but infrequent condition.

**Ethics and dissemination:**

UCES received a favourable ethical opinion from the South East Scotland Research Ethics Committee 02 (Reference: 18/SS/0047; IRAS ID: 233515). All spinal centres managing patients with CES in the UK will be encouraged to participate in UCES. Study results will be published in medical journals and shared with local participating sites.

**Trial registration number:**

ISRCTN16828522; Pre-results.

Strengths and limitations of this studyThis UK-wide study will be the largest prospectively established cohort of patients with cauda equina syndrome (CES).The collection of detailed clinical data will describe the range of presentations treated as CES in the UK in current practice and allow stratification of findings by clinical presentation.Validated outcome measures will be used to assess pain, disability, and bladder, bowel and sexual functions 1 year after treatment.Participant identification and recruitment will be efficiently carried out using trainee research networks to identify participants when referred urgently to specialist spinal centres.The relationship of timing of investigation and decompression to patient outcome will be limited by patient and clinician reporting of the timing of symptom onset.

## Introduction

Cauda equina syndrome (CES) is a rare but potentially devastating condition caused by compression of the cauda equina nerve roots. This most commonly occurs due to a prolapsed intervertebral disc. The clinical syndrome includes any of bilateral sciatica, saddle anaesthesia, bladder, bowel or sexual dysfunction.^1–3^ The disabling nature of these symptoms causes significant medical and social morbidity and high healthcare and social-care costs. In addition, litigation related to the management of CES leads to significant medicolegal workload and costs.^1 4 5^

Due to the consequences of CES for patients and society, several groups have issued clinical guidance on standards of care for CES.^1 6–8^ However, the evidence base for current clinical guidance consists of small retrospective single-centre case series.^1 9 10^ Even systematic reviews of outcomes in CES have included relatively few patients, with the largest including 464 patients.^9 11^ Lack of a clear definition of CES has hampered comparative analysis of historical studies, and different interpretations of available evidence have been offered.^10 12^ A diagnosis of CES encompasses patients presenting with mild to severe urinary and bowel symptoms, perineal or perianal numbness, sexual function disturbance or bilateral sciatica, and patients may also experience lower limb weakness, numbness or unilateral sciatica.^2 3 13^ Outcomes for different presentations vary and accurate division by presentation may help to clarify the understanding of outcome studies and develop care standards appropriate to the presentation.^1 14^

Retrospective case series in the UK have identified approximately 15–31 patients per year per specialist neurosurgical or spinal centre with confirmed CES.^3 13 15 16^ Published estimates of the incidence of CES are fewer than one case per 100 000 population.^17 18^ However, in 2010–2011 in England, 981 surgical decompressions were performed for CES,^19^ and the population was estimated at 52 234 000^20^ giving an incidence of 1.9 per 100 000. Therefore, there may be over 1000 patients managed for CES in the UK each year. Accurate data on the presentation and management of these patients would establish current management plus adherence to and feasibility of care-quality statements, as well as potentially informing the revision of guidance based on accurate and current data.

The British Neurosurgical Trainee Research Collaborative (BNTRC) has previously successfully used a network of neurosurgical trainees across the UK and Ireland to identify cases via local tertiary referral systems in conditions such as chronic subdural haematoma.^21^ As CES is managed in the UK by specialist spinal services, similar case ascertainment via specialist referral systems to neurosurgical, orthopaedic or joint spinal services provides a method of accurately identifying patients with CES during hospital admission. We propose to carry out the first national cohort study of the presentation and management of CES in the UK and establish the largest prospective series of patients with CES. This will provide data on CES incidence, epidemiology, presentation, management and outcomes. This will inform the development of clinical guidance and identify areas for future research in CES.

This prospective observational cohort study aims to:Identify the number of cases of CES in the UK in all collaborating centres.Describe the presenting symptoms and signs in patients with CES.Describe the pathways of presentation to specialist spinal services for patients with CES in the UK.Describe the type, timing and findings of investigations in patients with CES.Describe the medical and surgical management of CES.Compare current practice to standards of care for CES.Describe clinical outcomes for patients with CES using validated patient reported outcome measures stratified by presentation, investigation findings and management.Demonstrate the ability of neurosurgical and orthopaedic surgical trainee networks to collaborate successfully on a prospective cohort study.

## Methods and analysis

Understanding Cauda Equina Syndrome (UCES) is a prospective cohort study of patients with confirmed CES managed at specialist spinal centres in the UK. Cases will be identified by neurosurgical or orthopaedic trainees in each specialist centre through daily screening of tertiary referrals and admissions to specialist spinal services. All patients managed as CES by the treating team will be included in this study.

Data regarding timing and type of symptom onset, referral, investigation, management and outcome will be recorded anonymously on a secure database by the local trainee investigator during the patient’s hospital admission and after discharge. Patients' consent will be sought for the use of their data and they will be asked to complete patient-reported outcome measures representing their condition before surgery and up to 1 year after surgery. Imaging at presentation will also be collected. This data will be compared with care quality statements and published outcome data for CES. This is an observational study. No changes to routine patient care will occur during this study.

### Participant selection

The study will recruit patients for 1 year. Cases will be identified from admissions to spinal units between 1 June 2018 and 31 May 2019. The last 1-year follow-up assessments will be sent to participants on 31 May 2020.

For inclusion in this study, the patient must:Be over 18 years old.Be admitted to a specialist spinal service in the UK between 1 June 2018 and 31 May 2019.Have capacity to provide informed consent for participation in this study.Have a diagnosis of clinical CES and structural compression of the cauda equina on imaging as determined by the treating clinician.Clinical CES includes any of : altered saddle sensation; bladder dysfunction; bowel dysfunction; sexual dysfunction; or bilateral sciatica. This should be associated with radiological compression of the cauda equina. The cauda equina compression can be due to any cause, including but not limited to disc, tumour or infection.

There is no upper age limit as we aim to establish the demographics of those presenting with CES.

The exclusion criteria are:Children under 18 years of age.Patients undergoing emergent decompression for unilateral motor or sensory symptoms (such as foot drop), without clinical evidence of CES.Patients referred with suspected CES where the diagnosis is not confirmed;for example, patients with clinical symptoms and signs of CES but without radiological evidence of cauda equina compression.Patients not admitted to participating spinal centres in the UK.Patients admitted to a participating spinal centre before 1 June 2018 or after 31 May 2019.Patients who are unable to provide informed consent for participation in this study.

Capture-recapture methods will be used to ensure complete case ascertainment. In December 2018, June 2019 and December 2019 all local investigators will check their case ascertainment by asking their local coding departments for all discharges coded as CES using the diagnostic code from the International Classification of Diseases, 10th Revision (ICD-10) G83.4 Cauda Equina Syndrome. Any additional patients identified through this method that meet the inclusion criteria will be invited to participate.

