### Data collection

Data relating to presentation, hospital admission, investigations and follow-up will be collected by the local trainee investigator. Data will be collected from the patient’s notes, through routine interaction with the patient as part of clinical care, and through interaction with other staff members caring for the patient. All clinical and demographic information collected for this study by the local investigators will be collected routinely. No extra assessments will be performed.

Study participants who have consented to participate will also be asked to fill out details about their patient journey, their symptoms, patient reported outcome measures and service usage. These will be collected electronically and anonymously via the electronic database and linked to the patient record. Patient reported outcome measures will include visual analogue scores for back and leg pain plus relevant sections of the Oswestry Disability Index,^22^ the neurogenic bowel dysfunction score,^23^ the short form incontinence questionnaire^24^ and the Arizona sexual experiences scale.^25^

All patients who are eligible for inclusion in the study will have basic anonymous clinical data collected as part of the screening log to establish participation rates and incidence at each centre. This will allow accurate assessment of the incidence of CES. Patients who do not wish to participate in the study will not be contacted further for the completion of patient reported outcome measures.

The timing and type of clinician reported and patient reported data that will be collected for UCES is shown in figure 1:Study flow diagram.

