### Data analysis

This study aims to establish the number of patients presenting with CES in the UK over 1 year. We expect approximately 20 patients per spinal centre per year depending on the population served and a total of approximately 600–1000 patients in 1 year across the UK. The incidence of CES will be established based on the number of patients identified at each unit and the catchment population of that unit. If all units in the UK participate, incidence will be calculated based on the UK population estimates. Incidence will be calculated from all patients identified as being eligible for the study from referral screening and local coding departments, even if they do not consent for further participation.

A descriptive analysis of the clinical and demographic characteristics of presenting symptoms, signs and outcomes of patients with CES will be performed. This will be determined from both clinician-reported and patient-reported data. CES incidence and characteristics will be broken down into categories such as suspected CES, incomplete CES, with retention CES and early CES, based on the clinical data. The categorical and quantitative findings on imaging will also be described. Methods of patient presentation to specialist services will be described. Type, timings and findings of investigations in patients presenting via different routes will be compared. The investigation and management of patients with CES will be described and compared with that laid out in current care quality standards. Proportions meeting the standards will be reported. Patient outcomes will be assessed and analysed using both clinician-reported and patient-reported outcome measures at 6 months and 1 year. Patient outcomes will be stratified by demographics, presenting features, causative pathology, timing and findings of investigations, and timing and type of surgery. Patient usage of healthcare services over the year following diagnosis and management of CES, will be assessed using both patient-reported service usage and electronic records.

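### Capture-recapture is said to make ascertainment complete, but the incidence numerator is most naturally the union of two lists, so the case count is a minimum that gets reported without any estimate of completeness

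*Protocol article*

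**What the plan says.** The first list comes from trainees at each centre, who find cases "through daily screening of tertiary referrals and admissions to specialist spinal services" (Methods and analysis). The second comes from three checks, in December 2018, June 2019 and December 2019. At each one local investigators verify their ascertainment by "asking their local coding departments for all discharges coded as CES using the diagnostic code" G83.4 (Participant selection).

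The same section gives the purpose of the second list: "Capture-recapture methods will be used to ensure complete case ascertainment". It also gives the use: "Any additional patients identified through this method that meet the inclusion criteria will be invited to participate".

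The Data analysis section fixes the numerator: "Incidence will be calculated from all patients identified as being eligible for the study from referral screening and local coding departments", with non-consenters kept in. The rate is formed "based on the number of patients identified at each unit and the catchment population of that unit", or from UK population estimates if every UK unit joins. Of the screening log on all eligible patients, the Data collection section says: "This will allow accurate assessment of the incidence of CES".

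No section uses the overlap between the two lists.

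**The concern.** Capture-recapture is an estimation method. From the number of cases on list 1 only, list 2 only and both, it infers how many are on neither. The article names the method, gives it a purpose it cannot serve, and describes a procedure that only merges the lists. The step that would use the overlap does not appear.

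For eligible cases the direction is known. A union cannot exceed the true number, and it falls short whenever any case escaped both lists. Incidence is a planned output that the article expects to be accurate. If the observed figure came out low, a reader could not tell a lower frequency of the condition from missed cases, although the study would have had the data to help separate them.

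Timing matters too. If patients found through coding are merged without a source label, or if cases found by screening are never checked for presence on the coding list, the overlap may not be recoverable afterwards.

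**Working it through.** **The article's own figure.** The Introduction gives 981 decompressions in a population of 52 234 000: 981 / 52 234 000 × 100 000 = 1.878, which rounds to the stated 1.9 per 100 000. It reproduces. It is used below only to put the losses on a familiar scale.

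**Inputs.** The two lists and the union numerator come from the article. It gives no sensitivities and no information on dependence, so all of these are assumptions:
- screening sensitivity s1 and coding sensitivity s2: 95%/90%, 85%/65%, 80%/50%;
- odds ratio between the lists: 1 (independent), or 3 as an illustration of positive dependence.

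**Formulas.** Let p11 be the share of eligible cases on both lists.
- Independent lists: p11 = s1·s2, so the share on neither is (1 − s1)(1 − s2).
- Odds ratio 3: p11 is the smaller root of 2p² − [1 + 2(s1 + s2)]p + 3·s1·s2 = 0, and the share on neither is 1 − s1 − s2 + p11.
- Expected union = N × (1 − share on neither).
- Chapman estimate = (n1 + 1)(n2 + 1)/(m + 1) − 1, where n1 and n2 are the list sizes and m the number on both.

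**Independent lists.**
- 95%/90%: 0.05 × 0.10 = 0.5% missed.
- 85%/65%: 0.15 × 0.35 = 5.25% missed.
- 80%/50%: 0.20 × 0.50 = 10% missed.

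**Odds ratio 3, worked for 85%/65%.** 2p² − 4p + 1.6575 = 0 gives p11 = (4 − √2.74)/4 = 0.586. The share on neither is 1 − 1.50 + 0.586 = 8.6%. With N = 1000, Chapman is 851 × 651 / 587.2 − 1 ≈ 942.5, about 5.7% low.

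**Results for N = 1000 true eligible cases.**

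| s1/s2 | Odds ratio | Missed by union | Union | Chapman |
|---|---|---|---|---|
| 95%/90% | 1 | 0.5% | 995 | 1000 |
| 95%/90% | 3 | 1.2% | 988 | 992 |
| 85%/65% | 1 | 5.25% | 948 | 1000 |
| 85%/65% | 3 | 8.6% | 914 | 942 |
| 80%/50% | 1 | 10.0% | 900 | 1000 |
| 80%/50% | 3 | 14.2% | 858 | 905 |

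On the rate scale with independent lists, a true 1.9 per 100 000 would be reported as 1.9 × 0.995 = 1.89, 1.9 × 0.9475 = 1.80 and 1.9 × 0.90 = 1.71.

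The Chapman estimate recovers the total when the lists are independent. With an odds ratio of 3 it stays about 0.8%, 5.7% and 9.5% low in the three scenarios. That is nearer the truth than the union each time, but not fully corrected.

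**The case against.** The best defence is that the numerator sentence exists to keep non-consenters in the count, and that it does not exclude an adjustment, because a two-source estimate is also calculated from those two lists. The choice of estimator is commonly left to a full protocol or SAP, and neither is shown. This stands in part: a fuller document could add the estimator, so its absence alone would not be a finding. But the article goes beyond silence. It states a purpose that no second list can fulfil, describes a procedure that only adds patients, and gives a numerator that reads most simply as the union.

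It is also fair that the aims on presentation, pathways, management, standards of care and outcomes are descriptive and need no estimate of unseen cases, and that a union is a valid minimum if labelled so.

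Several stronger inferences are tempting, and the document does not support them:
- *Missed cases are already visible in the figures.* The Introduction suggests "there may be over 1000 patients managed for CES in the UK each year", while the Data analysis section expects about 600–1000. The first rests on decompressions in England in 2010–2011. The second is a planning figure built on about 20 patients per centre, in a study that requires radiological compression and capacity to consent. Case definitions and periods differ, and 1000 lies within the planned range.
- *The lists must be dependent because both need admission to a participating unit and the diagnosis.* These are eligibility conditions that every target case meets, so they cannot create dependence within the target population. Dependence could arise otherwise, for instance if clear-cut presentations are easier both to spot at screening and to code, but the article does not establish it. The odds ratio of 3 is illustrative only.
- *The bias exceeds the stated uncertainty.* The article states no interval or precision for incidence, so there is nothing to compare with.
- *This undermines the first aim.* That aim is a count of cases in collaborating centres. Incidence is a planned output but is not worded as that aim.

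**Conclusion.** The point holds as a should-fix. The claim of completeness is wrong as worded, and the numerator as written treats eligible cases on neither list as zero. As far as ascertainment goes, the count is a minimum.

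The size is unknown. It rests wholly on assumed sensitivities: about 0.5% if both lists are very sensitive, and about 5–10% if they are moderate, with independent lists. Positive dependence would enlarge it.

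A reader might infer that the published incidence will be too low overall. That does not follow. An error in the catchment population, or cases wrongly judged eligible, could push the rate either way, so only the ascertainment component has a known direction.

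**What to change.** **Participant selection.** Replace the wording on ensuring completeness with *improve and estimate the completeness of case ascertainment*. Record prospectively, for every eligible patient including non-consenters, whether found by screening only, coding only or both. This means checking at each of the three coding reviews which screened cases also appear on the coding list, as well as which are new. Because the log on non-consenters is anonymous, the flag should be set locally at the centre.

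**Data analysis.** Report the union as the observed minimum incidence. Beside it give the two-source (Chapman) estimate with a 95% CI and a sensitivity analysis for dependence between the lists. Label the estimate a likely lower bound if dependence is positive, and do not describe it as a full correction.

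**Cost.** One extra flag per patient, some matching at each centre and a few lines of analysis, with no new patient contact. The estimate brings an independence assumption and a slightly wider interval. In a simulation with 1000 true cases, 85%/65% sensitivities and independent lists, its SD was about 10 cases, so ±1.96 × 10 ≈ ±20, or about 2%.

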### Data collection

Data relating to presentation, hospital admission, investigations and follow-up will be collected by the local trainee investigator. Data will be collected from the patient’s notes, through routine interaction with the patient as part of clinical care, and through interaction with other staff members caring for the patient. All clinical and demographic information collected for this study by the local investigators will be collected routinely. No extra assessments will be performed.

Study participants who have consented to participate will also be asked to fill out details about their patient journey, their symptoms, patient reported outcome measures and service usage. These will be collected electronically and anonymously via the electronic database and linked to the patient record. Patient reported outcome measures will include visual analogue scores for back and leg pain plus relevant sections of the Oswestry Disability Index,^22^ the neurogenic bowel dysfunction score,^23^ the short form incontinence questionnaire^24^ and the Arizona sexual experiences scale.^25^

All patients who are eligible for inclusion in the study will have basic anonymous clinical data collected as part of the screening log to establish participation rates and incidence at each centre. This will allow accurate assessment of the incidence of CES. Patients who do not wish to participate in the study will not be contacted further for the completion of patient reported outcome measures.

The timing and type of clinician reported and patient reported data that will be collected for UCES is shown in figure 1:Study flow diagram.

